### 3.3.2 Standard of care(SOC)

Provide optimal support and medication in accordance with relevant latest clinical guidelines.

### 3.3.3 Intervention assignment

This study is an open-label, dose-escalation, single-armed phase I trial. In this study, a total four dose groups ( $5.0 \times 10^7$  cells,  $1.0 \times 10^8$  cells,  $1.5 \times 10^8$  cells,  $2.0 \times 10^8$  cells) are set up, dose escalation will be performed according to the "3+3" rule, each subject will be only entered into one corresponding dose group. See Section 3.8 for details.

## 3.4 Outcomes

### 3.4.1 Primary outcomes

The primary outcomes are the incidence of adverse events and the change in the Model for End-stage Liver Disease (MELD) score from baseline to the 28th day after the intervention.

### **3.4.2 Secondary outcomes**

The secondary outcomes include:

1. Change in the MELD score from baseline to the score at 3 days, 7 days, 14 days, 3 months, 6 months, 9 months, 12 months, 5months, 18 months and 24 months after the intervention
2. Incidence of each complication associated with decompensated cirrhosis
3. Liver transplant-free survival
4. Incidence of liver failure
5. Plasma albumin (ALB) level
6. Plasma prealbumin (PALB) level
7. Total bilirubin (TBIL)
8. Serum cholinesterase (CHE)
9. Prothrombin time (PT)
10. Child-Turcotte-Pugh (CTP) score
11. EuroQol Group 5-Dimension Self-Report Questionnaire (EQ-5D) scale score
12. Incidence of liver cancer
13. Chronic Liver Disease Questionnaire (CLDQ) score

### **3.5 Participant timeline**

## Protocol

### Assessment schedule for the patients with decompensated cirrhosis

|                                                 | Screening    | Period of treatment and observation period |              |              |               |                | Long-term follow-up |         |         |          |          |          |          |          |
|-------------------------------------------------|--------------|--------------------------------------------|--------------|--------------|---------------|----------------|---------------------|---------|---------|----------|----------|----------|----------|----------|
| Timepoint                                       | Day -21 to 0 | Day 1 ±0 day                               | Day 3 ±0 day | Day 7 ±0 day | Day 14 ±1 day | Day 28 ±3 days | Month 3             | Month 6 | Month 9 | Month 12 | Month 15 | Month 18 | Month 21 | Month 24 |
|                                                 |              |                                            |              |              |               |                | ±7 days             | ±7 days | ±7 days | ±7 days  | ±7 days  | ±7 days  | ±7 days  | ±7 days  |
| Enrollment and informed consent                 | ×            |                                            |              |              |               |                |                     |         |         |          |          |          |          |          |
| Screening table                                 | ×            |                                            |              |              |               |                |                     |         |         |          |          |          |          |          |
| Demographic data                                | ×            |                                            |              |              |               |                |                     |         |         |          |          |          |          |          |
| Allergies and family history                    | ×            |                                            |              |              |               |                |                     |         |         |          |          |          |          |          |
| Past medical history and treatment history      | ×            |                                            |              |              |               |                |                     |         |         |          |          |          |          |          |
| Existing disease and concomitant treatment      | ×            |                                            |              |              |               |                |                     |         |         |          |          |          |          |          |
| Vital signs                                     | ×            | ×                                          | ×            | ×            | ×             | ×              | ×                   | ×       | ×       | ×        | ×        | ×        | ×        | ×        |
| Physical examination                            | ×            | ×                                          | ×            | ×            | ×             | ×              | ×                   | ×       | ×       | ×        | ×        | ×        | ×        | ×        |
| Hepatitis B blood test/
HCV antibody         | ×            |                                            |              |              |               |                |                     | ×       |         | ×        |          | ×        |          | ×        |
| HIV/TP antibody                                 | ×            |                                            |              |              |               |                |                     | ×       |         | ×        |          | ×        |          | ×        |
| Blood routine test                              | ×            | ×                                          | ×            | ×            | ×             | ×              | ×                   | ×       | ×       | ×        | ×        | ×        | ×        | ×        |
| Urine routine test                              | ×            | ×                                          |              |              | ×             | ×              | ×                   | ×       | ×       | ×        | ×        | ×        | ×        | ×        |
| Urine pregnancy test                            | ×            |                                            | If necessary |              |               |                |                     |         |         |          |          |          |          |          |
| Stool routine test + occult blood               | ×            | ×                                          |              |              | ×             | ×              | ×                   | ×       | ×       | ×        | ×        | ×        | ×        | ×        |
| Blood biochemistry test                         | ×            | ×                                          | ×            | ×            | ×             | ×              | ×                   | ×       | ×       | ×        | ×        | ×        | ×        | ×        |
| Coagulation function test                       | ×            | ×                                          | ×            | ×            | ×             | ×              | ×                   | ×       | ×       | ×        | ×        | ×        | ×        | ×        |
| Blood ammonia                                   | ×            | ×                                          | ×            | ×            | ×             | ×              | ×                   | ×       | ×       | ×        | ×        | ×        | ×        | ×        |
| AFP                                             | ×            | ×                                          |              |              | ×             | ×              | ×                   | ×       | ×       | ×        | ×        | ×        | ×        | ×        |
| Electrocardiogram                               | ×            | ×                                          |              | ×            | ×             | ×              | ×                   | ×       | ×       | ×        |          | ×        |          | ×        |
| Chest X-ray or CT                               | ×            |                                            |              |              |               |                |                     |         |         | ×        |          |          |          | ×        |
| Abdominal ultrasound examination                | ×            | ×                                          |              |              |               | ×              | ×                   | ×       | ×       | ×        | ×        | ×        | ×        | ×        |
| Gastroscopy                                     | ×            |                                            |              |              |               |                |                     | ×       |         | ×        |          | ×        |          | ×        |
| Elastography                                    | ×            |                                            |              |              |               |                | ×                   | ×       | ×       | ×        | ×        | ×        | ×        | ×        |
| Upper abdominal CT/MRI plain scan + enhancement | ×            |                                            |              |              |               |                |                     | ×       |         | ×        |          | ×        |          | ×        |

## Protocol

|                                                                 |   |   |   |   |   |   |   |   |   |   |   |   |   |   |
|-----------------------------------------------------------------|---|---|---|---|---|---|---|---|---|---|---|---|---|---|
| MELD score                                                      | x | x | x | x | x | x | x | x | x | x | x | x | x | x |
| Child–Pugh score                                                | x | x | x | x | x | x | x | x | x | x | x | x | x | x |
| QoL scale                                                       | x | x |   | x | x | x | x | x | x | x | x | x | x | x |
| Collection of samples for omics research (blood sample + stool) |   | x | x | x | x | x | x | x | x | x | x | x | x | x |
| Infusion records                                                |   | x |   |   |   |   |   |   |   |   |   |   |   |   |
| Adverse events                                                  | x | x | x | x | x | x | x | x | x | x | x | x | x | x |
| Concomitant medication/treatment                                | x | x | x | x | x | x | x | x | x | x | x | x | x | x |

### **3.6 Sample size**

This is a proof-of-concept study. A total of 3–6 patients will be recruited for each dose cohort, comprising low, medium, high and super high-dose groups, denoted as cohorts 1, 2, 3 and 4, with three patients in each cohort initially. The additional patients will be added to the cohort if DLT is presented. A total of 12–24 patients will be recruited for the study. [19].

### **3.7 Recruitment**

Patient will be recruited from The Fifth Medical Center of PLA General Hospital. No other recruitment strategy (e.g., advertisement) will be adopted in this study.

### **3.8 Allocation and product management**

#### **3.8.1 Allocation**

This study is an open-label, dose-escalation, single-armed phase I trial. In this study, a total of four dose groups ( $5.0 \times 10^7$  cells,  $1.0 \times 10^8$  cells,  $1.5 \times 10^8$  cells,  $2.0 \times 10^8$  cells) are set up, dose escalation will be performed according to the "3+3" rule, each subject will be only entered into one corresponding dose group.

#### **3.8.2 Dose escalation and dose-limiting toxicity**

The single dose-escalation scheme, denoted as S-1, will be as follows 3+3: cohort 1 ( $5.0 \times 10^7$  cells), cohort 2 ( $1.0 \times 10^8$  cells), cohort 3 ( $1.5 \times 10^8$  cells) and cohort 4 ( $2.0 \times 10^8$  cells). Each patient will be observed for 3days for signs of dose-limiting toxicity (DLT) before another patient in the same cohort can receive treatment. The last patient of each cohort will be observed for 7days before the next cohort with a higher dose can start to receive treatment. The first three patients in a cohort will be observed to determine the next action. If one of the three patients shows signs of DLT, the next three patients in the cohort will be treated with the same dose. If two or more patients in any cohort show signs of DLT, then the study will be concluded. The study will only proceed to the next cohort if none of the first three patients shows signs of DLT after the outlined observation periods have elapsed or if only one out of the six patients in a cohort shows signs of DLT. The specific rules for dose escalation can be found in figure1.

The first dose of UC-MSCs in cohort 1 (three patients initially) will be  $5.0 \times 10^7$  cells. The maximum-tolerated dose (MTD) is determined as the highest dose that induces DLT in no more than one patient among the extended cohort of six patients. Patients will be recruited into four cohorts and will begin dosing at successively higher doses until the MTD is established or up to a dosage of  $2.0 \times 10^8$  cells.

[figure not shown]

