**Figure 1 Dose escalation flowchart**

### 3.8.3 Assessment of DLT and MTD

DLT will be evaluated according to the National Cancer Institute Common Toxicity Criteria (NCI-CTC) 5.0 ([https://ctep.cancer.gov/protocoldevelopment/electronic\\_applications/ctc.htm](https://ctep.cancer.gov/protocoldevelopment/electronic_applications/ctc.htm)). DLT is defined as any grade 4 hematological toxicity; grade 3 thrombocytopenia with hemorrhage; grade 3 or greater nausea, vomiting or, diarrhea or any grade 3 or greater treatment-related non-hematological toxicity (excluding alopecia and fatigue). Groups of three patients will be recruited at a time and allocated to their respective cohorts, starting with the lowest dose. For each cohort, one patient will be given the treatment at first and then observed for 3 days for signs of DLT. The next patient's treatment will only begin after the first patient has undergone 3 days of observation. The treatment of another cohort start after the previous cohort has experienced at least 7 days of observation.

The trial will proceed as follows to ensure safe dose escalation and determine the MTD: (1) If there is no DLT observed in all three patients of a cohort, the trial will proceed to the next dose cohort; (2)

If one of the three patients of a cohort experiences DLT, then three more patients will be included and tested in this dose cohort. If still only one of the six patients experiences DLT, the trial will proceed to the next dose cohort. However, if two or more of the six patients experience DLT, the previous dose will be considered as the MTD; (3) If two or all three of the three initial patients experience DLT in a cohort, the MTD will remain undetermined.

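### MSC-DLC-1a: after one DLT in three, the visible text lets patient 4 be dosed on a 3-day wait, before patient 3's Day 7 tests, so a provisional 1/3 may prove to be 2/3

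*Supplement*

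**What the plan says.** All references are to the MSC-DLC-1a protocol unless 1b is named.

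- **Within a cohort (3.8.2):** "Each patient will be observed for 3days for signs of dose-limiting toxicity (DLT) before another patient in the same cohort can receive treatment".
- **Between cohorts (3.8.2):** "The last patient of each cohort will be observed for 7days before the next cohort with a higher dose can start to receive treatment". Section 3.8.3 repeats this: "The treatment of another cohort start after the previous cohort has experienced at least 7 days of observation".
- **The decision on the first three (3.8.2):** "The first three patients in a cohort will be observed to determine the next action". No duration is given.
- **Expansion (3.8.2):** "If one of the three patients shows signs of DLT, the next three patients in the cohort will be treated with the same dose".
- **Stopping (3.8.2):** "If two or more patients in any cohort show signs of DLT, then the study will be concluded".
- **MTD (3.8.3):** branch (2), which starts from one DLT in the first three, says: "However, if two or more of the six patients experience DLT, the previous dose will be considered as the MTD". Branch (3) says: "If two or all three of the three initial patients experience DLT in a cohort, the MTD will remain undetermined".

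The assessment schedule in 3.5 has blood count, biochemistry and coagulation on Day 3 and Day 7, with no visit between them. After Day 1, the next electrocardiogram is on Day 7. No DLT evaluation window is named. Figure 1, the escalation flowchart, is not reproduced in the text available.

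**The concern.** Expansion patients belong to the same cohort at the same dose, so neither 7-day statement reaches them. The plan asks for a week of observation before raising the dose. It does not clearly ask for a week before treating more patients at a dose that has just caused a DLT.

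The choice between expanding (1/3) and stopping (2/3 or more) can therefore be made while patient 3 has only 3 days of follow-up and has not had the Day 7 tests. Those tests bear on the DLT definition, which includes grade 4 hematological toxicity. At stake is the treatment of one or two more patients with decompensated cirrhosis at a dose where the stopping count has in truth been reached. The wording also leaves a reader unsure which MTD branch applies if the second DLT in the first three is seen only after expansion has begun.

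**Working it through.** **The plan's own figure.** Four cohorts of 3 to 6 patients give 4 × 3 = 12 and 4 × 6 = 24, which reproduces the stated 12-24.

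**Timeline.** Input: the 3-day wait in 3.8.2, at the fastest pace. Patients 1 to 6 are dosed on calendar days 0, 3, 6, 9, 12 and 15. The infusion is on study Day 1, so patient 3 (calendar day 6) has Day 3 on calendar day 8 and Day 7 on calendar day 12. Patient 4 may be dosed on day 9, which is 12 − 9 = 3 days before patient 3's Day 7 tests. This step needs the fastest pace but no DLT rate or window.

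**How many patients are exposed.** Assume a 7-day DLT window. The windows of patients 1-3 close on days 7, 10 and 13.
- Patient 4 (day 9): patients 2 and 3 are still open.
- Patient 5 (day 12): patient 3 is still open.
- Patient 6 (day 15): none is open.

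So at most two patients are dosed on a provisional 1/3. With a 3-day window the windows close on days 3, 6 and 9, and nobody is exposed. With a 14- or 28-day window all three expansion patients could be.

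**How often.** Let p be the DLT rate per patient and F_i the share of DLT onsets in patient i that have shown by day 9. Two onset assumptions give a range:
- uniform over 7 days: F = 1, 6/7, 3/7;
- 75% by day 3, the rest uniform: F = 1, 0.938, 0.75.

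Put a_i = p·F_i. Then:
- A = P(exactly one DLT seen by day 9) = Σ a_i·Π_{j≠i}(1 − a_j)
- B = P(exactly one seen and at least one more to come) = A − (Σ a_i)(1 − p)²
- Share of day-9 expansions resting on a true 2/3 or more = B/A

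Example with p = 0.20 and uniform onset: a = 0.200, 0.171, 0.086. A = 0.1515 + 0.1254 + 0.0568 = 0.334. Σ a_i = 0.457, so B = 0.334 − 0.457 × 0.64 = 0.041, and B/A = 0.123.

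| p | Onset | A | B (per cohort started) | B/A (per expansion) |
|---|---|---|---|---|
| 0.10 | 75% by day 3 | 0.223 | 0.0054 | 0.024 |
| 0.10 | uniform | 0.197 | 0.0115 | 0.058 |
| 0.20 | 75% by day 3 | 0.363 | 0.0191 | 0.053 |
| 0.20 | uniform | 0.334 | 0.0411 | 0.123 |
| 0.30 | 75% by day 3 | 0.433 | 0.0378 | 0.087 |
| 0.30 | uniform | 0.418 | 0.0819 | 0.196 |

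A separate simulation with uniform onset agrees. At p = 0.10, one extra patient is dosed in 0.9% of cohorts and two in 0.2%; at p = 0.20 the figures are 3.3% and 0.9%.

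**With the decision held.** Patient 4 moves from day 9 to day 6 + 7 = day 13, when all three windows have closed, and B = 0 at every p.

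**The case against.** **Figure 1 may settle it.** The flowchart could state when the 1/3 decision is made, and its absence here is no fault of the plan. This limits the point to the visible text. The point still rests on an explicit 3-day rule, which the flowchart would have to override.

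**The text may already imply full observation.** The first three are observed before the next action, and 3.8.2 mentions observation periods having elapsed. But the first sentence gives no length, and the second governs moving to the next cohort, not expansion.

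**The DLT window may be 3 days.** That is the only period 1a labels as watching for DLT. On that reading the exposure is zero. This stands, and is why every percentage is conditional.

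**Accrual will be slower.** There is one site, no advertising, and a screening period of up to 21 days with gastroscopy and CT or MRI. This also stands: once patient 4 is dosed 7 or more days after patient 3, the problem disappears under a 7-day window.

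**Detection does not depend on visits.** Adverse events are recorded continuously (3.11), and several listed DLTs are clinical. True, but laboratory toxicity is scheduled for detection on Day 3 and Day 7.

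**The MTD branches need not conflict.** Branch (2) opens with one DLT in three, so branch (3) can be read as governing whenever two of the first three have a DLT. That is the better reading. A reader might infer a contradiction, but the text supports only a request for clearer wording, and in cohort 1 there is no previous dose to name.

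**Conclusion.** The gap is real in the visible 1a text and minor. Under a 7-day window, the fastest pace and DLT rates of 0.10, 0.20 and 0.30, about 2-6%, 5-12% and 9-20% of expansions opened on day 9 would rest on a true 2/3 or more. Per cohort started, that is about 0.5-1.2%, 1.9-4.1% and 3.8-8.2%. The rates, the onset patterns and the window are assumptions; 1a gives none of them.

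Three stronger readings are not supported:
- **That an unsafe dose could be escalated.** A late second DLT still ends the study under 3.8.2, and escalation still waits 7 days after the last patient.
- **That the 3-day stagger is itself wrong because 1b waits 7 days between subjects.** 1b gives three infusions (Days 1, 7 and 14) and 1a gives one. The comparison shows that a 7-day wait is workable for this sponsor, no more.
- **That the exposure is much larger because late DLTs in patients 4 and 5 should be added.** That route leads to two of six, not two of the first three, and concerns the chosen stagger rather than the expansion decision.

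The recruitment status in section 1 reports that all 1a dose groups have completed 28 days after dosing. The benefit is to any remaining dosing or to reuse of the rule.

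**What to change.** In 3.8.2 and 3.8.3, state that the 0/3, 1/3 or 2/3-or-more decision, and dosing of patient 4, wait until the third patient has completed 7 days, including the Day 7 tests. In 3.8.3, add that branch (3) governs whenever two of the initial three have a DLT, whenever the second is seen. Check that Figure 1 agrees.

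Cost: a sentence in each section and one clause. At the fastest pace an expanded cohort runs on days 0, 3, 6, 13, 16 and 19 and ends its 7-day observation on day 26 instead of day 22, a delay of 4 days. Cohorts with no DLT lose nothing, because escalation already waits 7 days.

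A 7-day wait between patients 4, 5 and 6 is optional. It would add 4 days to each of two gaps and move the end to day 34, 12 days later than now. That is a trade-off for the investigators, not a correction.

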| Date of enrollment | March 22, 2023 (The first subject signed the informed consent form)                                                                                                                                                                                                                                                                                                                                                                                                                                                                                 |
| Target sample size | 12~24                                                                                                                                                                                                                                                                                                                                                                                                                                                                                                                                               |
| Recruitment status | Participants in all dose groups have completed 28 days of observation after the dose, and 2-year safety follow-up is ongoing. The trial finishing date is estimated as March 1, 2025                                                                                                                                                                                                                                                                                                                                                                |
| Primary outcomes   | The primary outcomes are the incidence of adverse events and the change in the Model for End-stage Liver Disease (MELD) score from baseline to the 28th day after the intervention                                                                                                                                                                                                                                                                                                                                                                  |

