### **3.10 Statistical considerations**

#### **3.10.1 Statistical methods**

Efficacy will be assessed according to the intent-to-treat (ITT) analysis principle, while safety will be assessed by analyzing adverse events within the cohorts and noting their category and severity. Continuous variables will be expressed as the mean with the standard deviation (SD). Categorical variables will be expressed as a number count together with the rate or composition ratio. The chi-square test or Fisher's exact test will be used to compare categorical variables between different doses used by the cohorts for evaluating efficacy. They will also be used to compare the rate of adverse events occurrence between cohorts to assess safety. The change in the patients' lab values in each cohort after treatment will also be described to explore any potential correlations

between these changes and the occurrence of adverse events. Continuous variables will be compared using the *t*-test. However, comparisons will be made using the Wilcoxon signed-rank test when analyzing changes in continuous quantitative variables before and after treatment. The 95% confidence interval (95% CI) will be calculated for the outcomes of the continuous variables. A more detailed plan for the statistical analysis will be formulated and finalized before the data gathering is finished for the study. This final plan will dictate the method and content of the study's statistical analysis.  $P < 0.05$  will be considered as showing statistical significance. All the statistical analyses will be performed using SAS 9.4 (Statistics Analysis System, Inc. Cary, NC, USA).

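### MSC-DLC-1a: the six-patient MTD definition does not cover a dose cleared on 0/3 that rule (2) can name, and rule (3) gives no MTD after 2/3 or 3/3 where 2 or more of 6 would give one

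*Supplement*

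**What the plan says.** All references are to the MSC-DLC-1a protocol in the Supplement.

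- **Definition, section 3.8.2.** The MTD is "determined as the highest dose that induces DLT in no more than one patient among the extended cohort of six patients".
- **When a cohort grows to six, sections 3.6, 3.8.2 and 3.8.3.** Each cohort starts with three patients. "The additional patients will be added to the cohort if DLT is presented". Sections 3.8.2 and 3.8.3 make the trigger one DLT among the first three. After 0/3 the trial moves to the next dose.
- **Two or more DLTs in a cohort, section 3.8.2.** The study ends. The text gives no step that returns to the lower dose.
- **Rule (2), section 3.8.3.** After an extension, "if two or more of the six patients experience DLT, the previous dose will be considered as the MTD".
- **Rule (3), section 3.8.3.** "If two or all three of the three initial patients experience DLT in a cohort, the MTD will remain undetermined". It is not limited to cohort 1.
- **Purpose and end point of escalation.** Section 3.8.3 gives its rules "to ensure safe dose escalation and determine the MTD". Section 3.8.2 continues dosing "until the MTD is established or up to a dosage of" 2.0 × 10^8 cells.
- **Status and later plan.** The trial summary reports: "Participants in all dose groups have completed 28 days of observation after the dose". Section 3.10.1 adds: "A more detailed plan for the statistical analysis will be formulated and finalized before the data gathering is finished for the study".

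**The concern.** Two separate faults appear when these sentences are read together.

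First, the definition asks for six patients, but six are treated only where a DLT has occurred. A dose with no DLT in three patients is the cleaner result, yet it is outside the definition. Rule (2) does not ask how the previous dose was cleared, so it can name exactly such a dose.

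Second, rule (3) gives no MTD after two or three DLTs among the first three patients, even where a lower dose has been cleared. If the same cohort had shown one DLT in the first three and at least one more in the next three, rule (2) would have named that lower dose. The observed rate is 33% to 67% in the second case (2/6 to 4/6) and 67% to 100% in the first (2/3 or 3/3). The result that is as toxic or more so therefore yields the weaker statement about the dose below.

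What is at stake is the dose statement in the report. In an open-label trial whose dosing is finished, an unclear rule leaves room to choose that statement after the DLT counts are known.

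**Working it through.** **Reproducing the plan's own figure.** Four cohorts of three give 4 × 3 = 12, and four of six give 4 × 6 = 24. This matches the stated 12 to 24 and confirms that a cohort without a DLT stays at three.

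**Setting the rules side by side.** For a stop in cohort 2, 3 or 4:

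| Dose above fails as | Previous dose cleared on | 3.8.2 on the previous dose | 3.8.3 | Result |
|---|---|---|---|---|
| 2 or more of 6 | 0/3 | not covered (three patients) | rule (2): it is the MTD | mismatch |
| 2 or more of 6 | 1/6 | it is the MTD | rule (2): it is the MTD | agree |
| 2/3 or 3/3 | 1/6 | it is the MTD | rule (3): undetermined | direct contradiction |
| 2/3 or 3/3 | 0/3 | not covered | rule (3): undetermined | no clash with 3.8.2, but out of line with rule (2) |

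A stop in cohort 1 has no lower dose, so no MTD is the correct statement there.

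**Size.** The documents give no DLT rate, so p is assumed: 0.05, 0.10, 0.20 and 0.30, the same in cohorts 3 and 4. The calculation is conditional on reaching cohort 4, because the trial summary says that all dose groups completed 28 days, read here as all four. With q = 1 − p:

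- a = P(2 or 3 DLTs in the first 3) = 3p²q + p³. Rule (3) applies.
- e = P(1 in the first 3, then at least 1 in the next 3) = 3pq²(1 − q³). Rule (2) applies.
- s = P(cohort 3 cleared on three patients, given that it cleared) = q³ / (q³ + 3pq⁵).
- Affected outcomes = a + e·s: undetermined, or cohort 3 named on three patients.

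| p | a | e | s | e·s | a + e·s |
|---|---|---|---|---|---|
| 0.05 | 0.0073 | 0.0193 | 0.8808 | 0.0170 | 0.0243 |
| 0.10 | 0.0280 | 0.0659 | 0.8045 | 0.0530 | 0.0810 |
| 0.20 | 0.1040 | 0.1874 | 0.7225 | 0.1354 | 0.2394 |
| 0.30 | 0.2160 | 0.2897 | 0.6940 | 0.2011 | 0.4171 |

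Example at p = 0.10: a = 3 × 0.01 × 0.9 + 0.001 = 0.028. Next, e = 0.243 × (1 − 0.729) = 0.0659. Then s = 0.729 / (0.729 + 0.1771) = 0.8045, and a + e·s = 0.028 + 0.0530 = 0.0810.

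The remaining stops, e(1 − s) = 0.0023, 0.0129, 0.0520 and 0.0887, are those where the rules agree.

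The direct contradiction between rule (3) and the definition needs a 1/6 dose just below. Its probability is a(1 − s) = 0.0009, 0.0055, 0.0289 and 0.0661, a small part of the total.

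If the rates rise over the four cohorts as 5%, 10%, 20% and 30%, the affected share is 0.2160 + 0.2897 × 0.7225 = 0.2160 + 0.2093 = 0.4253, close to the last row.

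**The case against.** The strongest reply is that the operative rules may not be visible. Section 3.8.2 refers to Figure 1 for the specific escalation rules, and the figure is not shown. A step there that fills the previous dose to six would bring rule (2) into line with the definition, and undetermined in rule (3) could then mean undetermined until that step is done. The sentence that concludes the study at two DLTs speaks against this but does not exclude it. So the point covers the written text only, and it would be wrong to say that the figure cannot reconcile it.

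Several stronger readings are tempting and are not supported:

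- **Rules (2) and (3) contradict each other.** They govern disjoint outcomes, and no single data set triggers both. They are inconsistent in what they conclude about the same lower dose.
- **After 0/3, 1/6, 0/3, 0/3 the plan makes cohort 2 the MTD.** This takes the definition alone. Section 3.8.2 also lets dosing end at 2.0 × 10^8 cells without an MTD, which is the natural reading of that sequence.
- **A cohort 4 cleared on 0/3 is itself an affected outcome.** Given that cohort 4 is reached, this has probability 86%, 73%, 51% and 34% at the four rates. The sensible report there is that the MTD was not reached, and the plan allows it. These figures are not a measure of harm.
- **Patients were put at risk.** Escalation and stopping are stated clearly. Only the naming of the MTD is affected.

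It is also fair to say that MTD is not among the 1a outcomes in section 3.4, unlike in 1b, and that dosing is over. If all four cohorts were treated, the naming conflict matters only if cohort 4 had two or more DLTs. All of this limits the consequence. It does not make the sentences agree.

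**Conclusion.** The point holds for the text as written and is minor. The definition in 3.8.2 leaves out doses that rule (2) can name. Rule (3) withholds an MTD above cohort 1 where rule (2) would give one, and it contradicts the definition outright only when the previous dose cleared on 1/6.

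Given that cohort 4 is reached, the affected outcomes have probability of about 2.4%, 8.1%, 24% and 42% at DLT rates of 5%, 10%, 20% and 30%. The lower figures apply if the product is well tolerated. These numbers rest on assumed rates, independent patients, and reading the trial summary as saying that all four cohorts were treated. Figure 1 or the detailed analysis plan, neither of which is shown, may already settle the matter.

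**What to change.** State one rule in the detailed analysis plan and make Figure 1 agree with it:

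1. The MTD is the highest dose cleared on 0/3 or on at most 1/6, below a dose at which two or more patients had a DLT.
2. Treat 2/3, 3/3 and 2 or more of 6 alike: stop escalation and name the previous dose. Declare no MTD only if this happens in cohort 1.
3. If 2.0 × 10^8 cells clears, report that the MTD was not reached and that this is the highest tested tolerated dose.
4. Report the DLT count and the number treated in each cohort, so that a dose resting on three patients is seen as such.

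The cost is a few sentences and no patients. The trial summary says that 2-year follow-up is ongoing, so on that status the analysis plan can still carry the rule. Because dosing is finished, the plan and the report should say that the rule was clarified after dosing.
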